#### LAB 2 (pre-intervention)

Having completed the monitoring phase, participants will then return to the laboratory for measurement of a series of fasted and postprandial outcomes. Once again, hydration status will be ascertained from a urine sample before body mass is measured. As discussed previously, if body mass differs from the value recorded in LAB 1 by more than 1.0 kg then participants will be asked to repeat the monitoring phase. Providing this criterion is satisfied, then fasting measurements of resting metabolic rate and substrate oxidation will be repeated before a cannula is fitted to an antecubital vein and a fasting venous blood sample is drawn. In order to examine changes at the tissue level, a subcutaneous adipose tissue biopsy will also be obtained from the abdominal region at this time. The last of these fasted measurements will be a set a visual analogue scales and computer-based tasks to assess perceived hunger, fullness, desire to eat and food preferences. This will then be followed by two sequential test meals. The first will feature indirect calorimetry measurements from expired gases, visual analogue scales/computer tasks, and venous blood samples, whereas the second will only involve sampling of arterialised venous blood. Figure 1b shows the sampling intervals for the various measurements. Blood samples will be used to examine both postprandial nutrient handling (e.g. glucose, insulin, triglyceride concentrations) and appetite regulation (e.g. ghrelin, peptide YY concentrations). To conclude, a DEXA scan will be performed to measure pre-intervention fat and lean tissue mass.

#### Intervention phase

During a 6-day rest following LAB 2, which is included to avoid prolonged periods of monitoring [46] and maintain the 4-week testing interval, participants will be randomised to one of the three parallel intervention arms outlined in Table 1. The three diet groups will last for 20 days each with transitions between 24-hour cycles occurring at 15:00 each day. Not only does this transition point allow the consumption of at least one main meal per day to aid motivation, but more importantly, it also ensures that the latter and more demanding part of the fast coincides with diurnal reductions in appetite to encourage adherence [47]. Furthermore, this structure still gives a full 24-hour fasting period, which is around double that achieved in most prior studies [8].

**Table 1 Tab1:** Intervention arms employed in the study protocol

Intervention	Description
Daily calorie restriction	Reduce normal intake by 25% every day
Intermittent fasting with calorie restriction	Alternate between 24-hour periods of fasting and feeding with 150% of normal intake on fed days
Intermittent fasting without calorie restriction	Alternate between 24-hour periods of fasting and feeding with 200% of normal intake on fed days

For the IMF groups, during fasted cycles, participants are only permitted water, herbal teas and black tea/coffee with no sugar (i.e. unsweetened energy-free drinks). During feeding cycles, and throughout the daily calorie restriction diet, participants will appropriately modify their normal diet to give 75%, 150% or 200% of their habitual daily energy intake (measured during monitoring phase) in accordance with the group they are assigned to. Participants will also continue to monitor their physical activity and energy intake over the first and last 6 days of the intervention period. In the context of physical activity, this is to examine behavioural adaptations to the different diets; therefore, participants are allowed to adjust the quantity of activity/exercise undertaken based on how they feel, but are instructed not to incorporate any unfamiliar activities. In contrast, measurements of energy intake will be used to monitor compliance with intake targets with feedback provided to maximise accuracy. It is anticipated that, for some participants, doubling the volume of their habitual diet to achieve the calorie target whilst maintaining macronutrient balance will not be feasible. In these circumstances, achieving the required calorie intake will take precedence over maintaining macronutrient balance, both of which will be reported in resulting publications.

#### LAB 3 (post-intervention)

Following the completion of 20 consecutive 24-hour dietary cycles, participants will be required to standardise their diet and activity levels for 1 day to match those reported in the lead up to previous lab sessions and eliminate any residual effects of the final diet period. As with LAB 1 and LAB 2, this will also involve avoiding caffeine, alcohol, smoking and strenuous exercise before completing an overnight fast (minimum 10 hours) and consuming 500 mL of water upon waking. At 07:30 ± 01:00, participants will return to the laboratory and repeat the protocol outlined earlier for LAB 2, thereby providing a pre–post comparison.

### Anthropometry

Having voided upon arrival, measurements of body mass will be taken to the nearest 0.05 kg (Weylux 424, UK) with participants wearing light clothing. Height will be measured using a wall-mounted stadiometer to the nearest 0.1 cm whilst participants stand with their heels and shoulders touching the stadiometer. Body composition will be assessed by means of a DEXA scan (Discovery W, Hologic, MA, USA) taken in a supine position. For this, participants will be asked to lie on the scanning table with their feet evenly spaced to either side of the midline. Arms will be placed by their sides and equidistant to the trunk with the hands pronated and fingers spread. All measurements will be made following a quality control scan of a spine phantom with known properties in accordance with the manufacturer’s instructions.

### Energy intake

Energy intake will be measured throughout both the monitoring and intervention phases by means of a weighed record of food and fluid intake. In the initial lab session, participants shall be provided with a set of compact kitchen scales (SmartWeigh^TM^ Pocket Pro, NY, USA) and a log book to record all food and drink items. In addition, a researcher will discuss best practice with them and emphasise the level of detail required. These weighed records will be analysed (Nutritics^TM^, Ireland) to yield values for energy and macronutrient intake with all records for a given participant analysed by the same researcher.

### Physical activity

Physical activity will be measured using Actiheart™ monitors (CamNtech, UK) that employ combined heart rate and accelerometry data to yield minute-by-minute estimates of physical activity energy expenditure and intensity under free-living conditions [43]. These monitors will be individually calibrated for each participant using an adapted version of the treadmill protocol described by Brage et al. [44]. Specifically, this involves completing four 3-minute stages of supervised incremental treadmill locomotion, namely level walking at 3.2 km/h, brisk level walking at 5.2 km/h, brisk graded walking at 5.8 km/h (+10%) and level running at a self-selected speed of 9.0–12.0 km/h. During the final minute of each stage, heart rate (RS400, Polar, Finland) and energy expenditure (indirect calorimetry of expired air samples) will be measured. This will yield a heart rate–physical activity intensity regression equation for each participant which accommodates the inter-individual differences in this relationship to dramatically improve concurrent validity [44]. However, participants can choose to omit the final stage (level running) if they do not feel able in order to avoid biasing the sample in favour of more formal exercisers. Furthermore, the treadmill protocol will also be ended prematurely if the participant asks to stop or if their heart rate exceeds 85% of their age-predicted maximum.

### Meal tests

In order to examine the impact of the interventions on nutrient handling and appetite regulation, in addition to any second meal effects [48], two successive meal tests will be completed in LAB 2 and LAB 3. Both meals will be tailored to provide one-third of resting metabolic rate as measured in the fasted state during LAB 2. The first meal (breakfast) will be in the form of a homogenous porridge meal (1.31 kcal/g; 59% carbohydrate, 29% fat, 12% protein) composed of golden syrup flavour instant oats (Sainsbury’s, UK), whole milk (Tesco, UK) and white granulated sugar (Silver Spoon, UK). This will be cooked in a microwave and cooled for 10 minutes before being consumed in its entirety within a designated 10-minute eating opportunity. This will be followed by a 3-hour postprandial period featuring venous blood samples (15, 30, 45, 60, 90, 120, 180 minutes), visual analogue scales (30, 60, 90, 120, 150, 180 minutes), computer-based food-choice tasks (45, 105, 165 minutes) and expired air samples (60, 120, 180 minutes).

By comparison, the second meal (lunch) will take the form of a liquid meal-replacement supplement (1.50 kcal/mL; 54% carbohydrate, 30% fat, 16% protein; Ensure Plus, Abbott Nutrition, OH, USA) which will be consumed following a blood sample within a 5-minute feeding window positioned 210 minutes after the consumption of the first meal. A 2-hour postprandial period will then follow in which arterialised venous blood samples will be drawn using the heated hand-box method (225, 240, 255, 270, 300, 330 minutes).

### Indirect calorimetry

Resting metabolic rate and substrate oxidation in both the fasted and postprandial state will be measured using indirect calorimetry of expired air samples [49]. In each instance, three consecutive 5-minute air samples will be collected using a mouthpiece and the Douglas bag method (Hans Rudolph, MO, USA) before analysis (Servoflex MiniHF 5200, Servomex, UK) and evacuation (Dry Gas Meter, Harvard Apparatus, MA, USA). Samples will be collected in accordance with best practice guidelines [50], with the values from two or more samples that agree to within 100 kcal/day averaged and used in further analysis [37], along with the corresponding substrate oxidation parameters. During the treadmill test for the calibration of activity monitors, a single 1-minute air sample will be collected per stage for which a facemask shall be used in place of the mouthpiece for participant comfort.

### Blood sampling

In LAB 2 and LAB 3, all blood samples will be procured by means of an intravenous cannula. At each sampling interval, the first 2 mL of the draw will be discarded as waste before a 5 mL sample is collected. This sample will then be dispensed in to an EDTA tube and centrifuged before the supernatant is aliquoted across three 1.5 mL tubes and stored at −80 °C pending subsequent analysis for plasma concentrations of nutrients (e.g. glucose, triglycerides) and regulatory hormones (e.g. insulin, leptin). In the fasted state, and at hourly intervals in each postprandial period, an additional 5 mL will also be drawn to quantify plasma concentrations of hormones implicated in appetite regulation (e.g. ghrelin, peptide YY). Once obtained, this additional 5 mL will be immediately transferred to an EDTA tube to which 50 μL of a 1.0 mM p-hydroxymercuribenzoic (PHMB) acid solution has been added. This will then also be centrifuged before 600 μL of the supernatant is removed and transferred to a sterile tube containing 60 μL of 1 M hydrochloric acid and centrifuged once again. The PHMB and acidified plasma samples will then be aliquoted into two separate 1.5 mL tubes and stored at −80 °C for later analysis. Following the draw of each blood sample, the cannula will be flushed with a 0.9% sodium chloride solution to keep it patent. All samples will be centrifuged (Biofuge Primo R, Heraeus, Germany) at 4 °C for 10 minutes at 3466×*g*.

### Adipose tissue biopsy

Adipose tissue biopsies will be obtained from the subcutaneous abdominal region. For this, a site 5 cm to the left or right of the umbilicus will be sterilised and anaesthetised (1% lidocaine hydrochloride without adrenaline, Hameln Pharmaceuticals, UK) before a sample is obtained using the needle aspiration method [51]. This sample will be cleaned on 100 nm gauze with a sterile 0.9% sodium chloride solution before being separated into aliquots of approximately 250 mg. One aliquot will be immediately disrupted in TRIzol (Invitrogen) using a hand-held homogeniser (Fisher Scientific, CA, USA) and frozen at −80 °C for subsequent analysis. The second aliquot will be immediately frozen at −80 °C. Biopsies obtained in LAB 2 and LAB 3 will be taken from opposing sides of the umbilicus.

### Urine collection

Urine samples will be collected at the outset of each lab session to ensure participants are similarly hydrated for repeated body mass measurements. The samples will be analysed on the day for osmolality, via the freeze-point depression method (Micro Osmometer 3300, Advanced Instruments, MA, USA) and specific gravity (SUR-NE Clinical, Atago, Tokyo). Furthermore, during the 3-hour postprandial period which follows the breakfast meals, total urine output will be collected into containers prepared with 5 mL of a 10% thymol–isopropanol solution. At the end of the 3-hour period, the total volume of urine will be measured with a 1 mL sample extracted and frozen at −80 °C for subsequent analysis of urine urea concentration, as an indicator of protein excretion, to calculate the contribution of protein oxidation to whole body energy metabolism.

### Appetite

Appetite will be measured using visual analogue scales [52] assessing hunger, stomach fullness, desire to eat, thirst and food preference (sweet, salty, savoury, fatty), and two computer-based tasks. For each of the visual analogue scales there will be a question (e.g. how hungry do you feel?) followed by a 100 mm visual scale with the extremes defined (e.g. not at all – as hungry as I have ever felt). Participants shall be asked to place a vertical line on the scale to denote their perception relative to the two extremes, with the distance from the zero point to the marked point measured and recorded by the same researcher for all scales.

The computer-based tasks are a two alternative forced choice task (2AFCT) and an ideal portion size task (IPST) [53]. The 2AFCT comprises a set of 18 foods which are individually photographed in an approximately standard portion on a white plate, or in a plain glass bowl placed on the white plate. In terms of nutrient composition and taste, there are six triplets of foods. The foods within each triplet have a very similar energy density and weight, and across the triplets energy density varies from 1.1 kcal/g to 5.0 kcal/g. Each triplet contains one sweet high-carbohydrate food, one non-sweet high-carbohydrate food and one non-sweet low-carbohydrate food. An example triplet is vanilla ice cream, Singapore noodles and stir-fry sauce, and tuna and mayonnaise. In the task, each food is paired side-by-side once with all of the other foods to give a total of 153 trials (the side on which the foods appears is randomised across trials). For each pair of foods, the participant indicates by depressing the left or right arrow-key on the computer keyboard which food they would ‘choose to eat right now’. Outcome measures are (1) proportion of trials on which a high-sweetness, high-carbohydrate food is chosen, (2) proportion of trials on which a low-sweetness, high-carbohydrate food is chosen, (3) proportion of trials on which a low-carbohydrate food is chosen, and (4) average energy content of the chosen foods for each of these categories. There is a ‘base rate’ for each category because, on some occasions, there will be a choice between two low-carbohydrate foods, for example, but these will differ in energy content/density. For the IPST [54], there are three test foods, vanilla ice cream, Singapore noodles and stir-fry sauce, and tuna and mayonnaise, which are photographed in portions ranging from 20 to 1000 kcal in 20 kcal increments (50 pictures in total). In each of three trials one of these foods is displayed in the middle of the computer screen. Depressing the left arrow-key causes the portion size to decrease (a smaller portion is displayed) whilst pressing the right arrow-key causes the converse. The pictures are loaded with sufficient speed that continuous depression of the left or right arrow key gives the appearance that the change in portion size is animated. Each trial starts with a different and randomly selected portion size. Participants are instructed to ‘Imagine you are offered this food right now. Use the left and right arrow keys to adjust the portion to show how much of it you would eat.’

These measures are designed to complement measures of hormones implicated in appetite control and account for any changes in how satiety signals are interpreted. Furthermore, the two computer tasks will determine whether the different interventions influence preference for sweet or non-sweet carbohydrates, or both. The visual analogue scales shall be completed in the fasted state and at 30 minute intervals following the breakfast meal in LAB 2 and LAB 3. The computer-based tasks will be completed in a fasted state and 45, 105 and 165 minutes after the breakfast meal.

### Data management

Upon providing informed consent, participants will be assigned with a unique identifier that will be used on all data collection documentation to preserve confidentiality. Data recorded in physical form will be digitised and stored in a central file that can only be accessed by the research team. Once a complete dataset has been compiled, manuscripts will be drafted and submitted for publication in appropriate peer-reviewed journals. The criteria that warrant an authorship in resulting publications will be addressed once data analysis has been completed. Once the results have been formally published the trial dataset will be released in anonymised form and an engagement event will be arranged to inform participants of the findings. Should any data or biological samples collected in the present study be needed for ancillary studies, appropriate consent will be sought from participants before proceeding.

A full risk assessment has been conducted by the research team and was subsequently approved by the research sponsor and the NHS Research Ethics Committee (Frenchay). Prior to enrolling, all participants will be fully informed of the potential risks associated with engaging in this study. In particular this will centre upon the symptoms they may experience as a result of prolonged fasting and dietary restriction (e.g. headaches, tiredness, hunger, irritability, spells of dizziness/faintness), as well as the risk of discomfort and infection that accompanies tissue biopsy and blood sampling procedures. Participants will be free to withdraw from the study at any time during their involvement. As neither participants nor researchers are blinded to trial allocation the research team will take responsibility for noting and reporting adverse events to the study sponsor and the ethics committee. Overall conduct of the trial, including adverse event reporting, data management protocols and researcher conduct, will be subject to biannual progress reports by the research sponsor. However, there is no intention to end the trial prematurely based in interim results which, together with the wider data monitoring framework, renders a data monitoring committee unnecessary. Any modifications to the study protocol will be submitted to the trial sponsor and NHS research ethics committee (Frenchay); if approved, publications and trial registrations will be updated accordingly.

### Data analysis

As outlined in the aims of the present study, the primary outcomes will explore the effects of the intervention on postprandial glucose/insulin responses (pre–post) and energy balance – reflected by changes in resting metabolic rate (pre–post), physical activity energy expenditure (monitoring–intervention) and postprandial thermogenesis (pre–post). Secondary outcomes will explore changes from pre- to post-intervention in body composition, substrate oxidation, lipid profile, leptin concentration, c-reactive protein concentration, adipose tissue gene expression, postprandial lipaemia and postprandial appetite regulation/perception. In addition, differences in physical activity intensity and dietary composition between the monitoring and intervention phases will be examined. As it is not the objective of this study to compare these differences between the cohorts, two sets of analyses will be conducted on a per protocol basis -– one for the lean cohort and one for the overweight/obese cohort. Both will centre upon a two-way mixed model analysis of variance featuring a factor for diet allocation and a factor for time-point. This will permit an examination of the effect of each diet on the outcomes of interest (i.e. pre vs. post/monitoring vs. intervention) and whether this effect varied between the three dietary conditions. Pre-existing differences between groups at baseline will be examined using a one-way analysis of variance featuring a factor for diet allocation. Significant differences emerging from these tests will be explored using appropriate post-hoc tests to adjust for multiple comparisons and isolate the source(s) of variance. In addition to these analyses at the group level, individual responses will also be closely scrutinised to examine whether outliers could be affecting the interpretation. Further analysis, such as sub-group analysis, may also be conducted in light of patterns emerging in the final dataset. Baseline characteristics of participants who withdraw during the intervention will also be compared against the final population using *t* tests. Statistical significance will be accepted at *P* < 0.05.

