## Methods

### Participants

To address these objectives two separate cohorts of 30–36 healthy adults who satisfy the inclusion/exclusion criteria outlined below will be recruited. One cohort will feature exclusively lean participants (body mass index (BMI) 20.5–25.0 kg/m^2^) and the other overweight/obese participants (BMI > 25.0 kg/m^2^). This will be confirmed using the fat mass index (FMI) obtained from a dual-energy x-ray absorptiometry (DEXA) scan, with values ≤ 7.5 kg/m^2^ and ≤ 11.0 kg/m^2^ classified as lean for males and females, respectively. In line with the objectives of this protocol the effects of IMF in these two cohorts will not be compared, instead they will be published as separate studies with matched methods to provide a thorough evaluation of the impacts of IMF in these two metabolically distinct populations.

Participants in each cohort shall then be allocated to one of three parallel intervention arms in a 1:1:1 allocation ratio using a stratified randomisation scheme. This will feature a factor for objectively measured physical activity level (PAL), which is calculated by dividing each participant’s total daily energy expenditure by their resting metabolic rate, to ensure an even distribution of lower activity (PAL < 1.75) and higher activity (PAL ≥ 1.75) participants in each condition. In accordance with best practice recommendations for randomised controlled trials [35], allocation concealment will be employed to minimise bias. The scheme will be generated by a senior author who is not involved in participant recruitment or management ([name]) using an electronic random number generator. Intervention allocation will be requested via email by those responsible for participant management (IT), with only the participant code, BMI/FMI and PAL being sent. As only the delivery team will engage with participants and know their corresponding code, whilst only the senior author knows the block sizes and sequences, it is not possible for the allocation to be reliably predicted or biased by either party. Full details of the overall randomisation scheme will be included in publications once all allocations are completed in order to prevent deciphering [36]. The protocol for these studies has received ethics approval from the National Health Service Research Ethics Committee (reference: 15/SW/0007) and has been registered at clinicaltrials.gov under reference number NCT02498002 (version: IMF-02, date: July 6, 2015).

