### Power calculation

The sample size for this study has been estimated using an a priori power analysis of studies employing similar durations of daily calorie restriction. Specifically, Friedlander et al. [39] observed a significant decline in resting metabolic rate following 21 days of daily calorie restriction (pre: 1898 ± 262 kcal/day, post: 1670 ± 203 kcal/day). Applying a two-tailed *t* test to these data suggests that 11 participants would be required to achieve 80% power when detecting such an effect at an alpha level of 0.05. Focusing instead on changes in postprandial glucose metabolism, Molfino et al. [40] reported a significant reduction in 2-hour post-bolus plasma glucose values during an oral glucose tolerance test following 10 days of daily calorie restriction (pre: 10.72 ± 3.56 mmol/L, post: 7.10 ± 2.96 mmol/L). In this instance, nine participants would be required to detect a comparable within-treatment effect with 80% power at an alpha level of 0.05. Collectively, this suggests that 9–11 participants will be required per group to establish within-treatment effects in the primary outcomes. However, given the potential for variability in the outcomes of interest, particularly when working with obese populations [16, 17], a more conservative requirement of 10–12 was decided upon. With 10–12 participants required in each of the three intervention arms, 30–36 lean participants and 30–36 overweight/obese participants will be sought in total, allowing examination of these two metabolically distinct populations to be kept separate. Recruitment will be conducted using adverts at local employers and media outlets, and will proceed on a rolling basis until an adequate sample size is reached. To minimise loss to follow-up emphasis will be placed on considering the demands of the study before enrolling and that feedback of personal results will only be available to those who complete all three lab sessions. In cases of withdrawal, additional participants will be sought to maintain statistical power; however, the point of withdrawal and the accompanying reason will be reported in a CONSORT flow diagram in subsequent publications.

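### The between-diet comparison is planned on change scores; adjusting for the baseline value and the PAL stratum would usually be more precise, by an amount that depends on an unstated pre–post correlation

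*Protocol article*

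**What the plan says.** The Data analysis section names the main model for each cohort: "Both will centre upon a two-way mixed model analysis of variance featuring a factor for diet allocation and a factor for time-point". It is to show the effect of each diet and "whether this effect varied between the three dietary conditions". Outcomes are compared pre to post, or monitoring to intervention, so there are two time-points. No baseline covariate and no PAL term is named.

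Baseline is handled separately: "Pre-existing differences between groups at baseline will be examined using a one-way analysis of variance featuring a factor for diet allocation". Significant results go to post-hoc tests. No change to the outcome analysis is attached to them.

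The Participants section says that each cohort is "allocated to one of three parallel intervention arms in a 1:1:1 allocation ratio using a stratified randomisation scheme", with a PAL factor "to ensure an even distribution of lower activity (PAL < 1.75) and higher activity (PAL ≥ 1.75) participants in each condition". PAL is therefore known for everyone randomised.

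The Power calculation section sizes each arm for within-treatment change. For resting metabolic rate it uses "pre: 1898 ± 262 kcal/day, post: 1670 ± 203 kcal/day" and arrives at 11 participants. For 2-hour glucose it arrives at 9. It then settles on 10–12 per arm.

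**The concern.** All three aims in the Background compare diets: intermittent fasting against daily restriction, and against eucaloric fasting. The diet-by-time term carries those comparisons. With two time-points it is algebraically a one-way analysis of variance of post minus pre.

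Subtracting baseline does adjust for it, but with a slope of 1. When the true regression slope is below 1, an arm that starts high by chance tends to fall back, and the change score counts that fall as a diet effect. With 10–12 per arm, chance imbalances are not small. A significance test of baseline differences does not repair this. After randomisation it can only flag chance, it has little power at this size, and nothing in the outcome analysis follows from it.

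What is at stake is the precision of the between-diet estimates, in a trial sized only for within-arm effects.

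**Working it through.** **Inputs from the protocol.** Resting metabolic rate: 1898 (SD 262) to 1670 (SD 203), difference 228 kcal/day. Two-hour glucose: 10.72 (SD 3.56) to 7.10 (SD 2.96), difference 3.62 mmol/L. Two-sided alpha 0.05, 80% power, 10–12 per arm, three arms. **Not stated:** the pre–post correlation ρ.

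**1. Reproduce the protocol's figures.** Paired t test (noncentral t), SD of change = √(s₁² + s₂² − 2ρs₁s₂).

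| ρ | n, metabolic rate | n, glucose |
|---|---|---|
| 0.3 | 14 | 12 |
| 0.5 | 11 | 9 |
| 0.7 | 8 | 7 |

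At ρ = 0.5 the SDs of change are 238 and 3.30, and the standardised changes are 228/238 = 0.96 and 3.62/3.30 = 1.10. The stated 11 and 9 are matched for ρ of about 0.48–0.54 and 0.47–0.55 respectively.

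**2. Size of chance imbalance.** Take a common SD of 234 kcal/day, since √((262² + 203²)/2) = 234. The SD of the difference between two arms' baseline means at 12 per arm is 234 × √(2/12) = 96. With equal SDs the regression slope is ρ, so an imbalance of 96 shifts the change-score contrast by (1 − 0.5) × 96 = 48 kcal/day. That is 48/228, about a fifth of the planning effect.

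**3. Large-sample gain.** With equal SDs, the variance of change is 2σ²(1 − ρ) and the ANCOVA residual variance is σ²(1 − ρ²). Their ratio is (1 + ρ)/2, so the reduction is (1 − ρ)/2, which is 25% at ρ = 0.5.

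**4. Small-sample cost.** Estimating k covariate slopes multiplies the variance by about 1 + k/(3n − 3 − k − 1).
- Baseline only (k = 1): 1 + 1/25 = 1.040 at 10 per arm; 1 + 1/31 = 1.032 at 12.
- Baseline plus PAL (k = 2): 1 + 2/24 = 1.083 at 10; 1 + 2/30 = 1.067 at 12.

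Net reduction = 1 − (1 + ρ)/2 × cost. The PAL column assumes that PAL explains nothing further.

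| ρ | baseline only | baseline + PAL |
|---|---|---|
| 0.5 | 22–23% | 19–20% |
| 0.7 | 12% | 8–9% |
| 0.8 | 6–7% | 2.5–4% |
| 0.9 | 1–2% | −3% to −1% |

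A simulation at 11 per arm and ρ = 0.5 gave 21% and 20%. PAL was balanced across arms there, so fitting it cost less than the formula charges.

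**5. Power for a 228 kcal/day between-diet contrast.** σ = 234, ρ = 0.5, pooled error degrees of freedom, unadjusted for multiple comparisons. The standard error of the change-score contrast is 234 × √(2/n). The adjusted one is that value times √(0.75 × cost).

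| n per arm | change score | baseline only | baseline + PAL |
|---|---|---|---|
| 10 | SE 104.6, 56% | SE 92.4, 66% | SE 94.3, 64% |
| 12 | SE 95.5, 64% | SE 84.1, 75% | SE 85.4, 73% |

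At ρ = 0.8 and 12 per arm, power is already 96% on change scores, and adjustment moves it by about one point or less.

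**The case against.** The planned test is valid and unbiased under randomisation, so this is a matter of efficiency. That stands.

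The correlation of 0.5 may be an artefact. The stated sample sizes also follow from dividing each difference by the pooled SD (0.973 and 1.106) and using the result as a paired effect size, which amounts to ρ = 0.5 when SDs are equal. It is then no evidence about how repeatable these outcomes are. That stands too, and is why the gain is given as a range.

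A reader might infer a saving of a quarter or more at no cost. The documents do not support that. With equal SDs, a 25% reduction needs ρ ≤ 0.5 even before the covariate cost, and ρ ≤ about 0.38–0.45 after it. The unequal SDs in the Power calculation section would give 45% (metabolic rate) and 40% (glucose) at ρ = 0.5. Those SDs come from calorie-restriction data, however, and applying them to all three diets, including eucaloric fasting, is an assumption.

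A reader might also infer that leaving PAL out makes the standard errors invalid. It does not: omitting a factor balanced by stratification leaves the estimates unbiased and tends to make standard errors conservative. PAL is total expenditure divided by resting metabolic rate, so it may add little once the baseline value of either is in the model. The article is also condensed and says only that the analysis centres on this model, so a missing covariate list alone would be a weak charge. What the article does fix is the form of the between-diet test.

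Finally, the sample size targets within-treatment change, which ANCOVA does not improve. This is correct and limits the point to between-diet contrasts.

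**Conclusion.** The point holds as a low-cost efficiency improvement to the between-diet comparisons. The planned analysis remains valid, and 10–12 per arm is not called into question by it.

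The 19–23% net variance reduction, worth about 9–11 points of power, rests on equal SDs, ρ = 0.5, a true between-diet difference as large as the planning change of 228 kcal/day, and a PAL term that explains nothing further. For outcomes with ρ near 0.9 the gain disappears and can turn slightly negative. No figure in the protocol supports a specific gain from PAL. The reason to include it is consistency with the randomisation, not a demonstrated saving.

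The baseline significance tests serve no purpose in a randomised comparison and can be replaced by description.

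**What to change.** For the between-diet comparisons, state that within each cohort the model is: post (or intervention) value = diet + baseline (or monitoring) value + PAL stratum (<1.75 / ≥1.75). Report adjusted between-diet differences with 95% confidence intervals. Describe baseline values by arm and drop the one-way analysis of variance on them. Within-arm pre–post changes can stay as planned.

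The cost is a sentence or two of wording and one or two error degrees of freedom out of 27–33. The variance charge for estimating the covariates is about 3–4% for baseline alone and up to 7–8% with PAL. No new data or participants are needed. The Trial status section reports recruitment as ongoing, so the change could be made before analysis.
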